### **Data management and monitoring**

All protocol-required information collected during the trial is entered in the case report form (CRF) by the investigator or a designated representative. Investigators are expected to complete documentation as soon as possible after the information is collected, preferably on the same day that a trial participant is seen for an examination, treatment or any other trial procedure. An explanation must be given for all missing data.

The completed CRF must be reviewed and signed by the investigator named in the trial protocol or by a designated sub-investigator. After keeping a copy at the trial center, the original CRF is sent to the IMBI for data entry. Double data entry is carried out at the IMBI to ensure correct transfer of data from the CRF to the database. Completeness, validity and plausibility of data are examined by validating programs that thereby generate queries, which need to be clarified by the investigator. At the end of the trial, the principle investigator will retain the original CRFs. All data are managed and analyzed at the joint unit of the Study Center of the German Surgical Society and IMBI in accordance with the current standard operating procedures of the IMBI.

Monitoring is carried out in accordance with ICH E6 (Good Clinical Practice) and standard operating procedures by the Coordinating Center for Clinical Trials, Heidelberg. Participating centers are activated with an initiation visit by the monitor, who will hand out the prepared investigator site file. All relevant trial issues are discussed and trial personnel is trained. Important issues controlled by the monitor are availability of written informed consent and compliance to inclusion and exclusion criteria, as well as documentation of primary endpoint and safety data. Regular contact by phone and/or email with all participating centers will enable the monitor to control the study progression, check adherence to the study protocol, and discuss problems related to the study. In addition, close-out visits are planned for each center.

### **Statistical consideration and sample size**

#### ***Hypothesis***

Within confirmation analysis, the null hypothesis tested is that there is no difference in the incidence of burst abdomen at 30 days postoperatively or incisional hernia within 12 months after emergency midline laparotomy between the two abdominal wall closure strategies under investigation.

#### ***Interim analysis***

When the study was planned, there existed no pilot data and there was no evidence with respect to the scientific question of the study [20]. Therefore, the values of the parameters required for sample size calculation (overall rate and treatment effect to be expected) were completely unknown. Within a fixed sample size design, it was hence uncertain whether the desired power would be achieved or not. For that reason, the study is performed with an adaptive interim analysis. This design allows early stopping of the trial or, if continued, modification of design characteristics - such as recalculation of the sample size - under control of the global type I error rate.

The implementation of the design is as follows: an adaptive interim analysis as described by Bauer and Köhne [21] will be performed after 80 evaluable patients have completed the 12 months follow-up. The global one-sided type I error rate of the trial is controlled by 0.025. This is achieved by implementing the following decision rules. The study is stopped after the interim analysis with acceptance of the null hypothesis if the one-sided *P*-value lies above 0.40, and with rejection of the null hypothesis if the one-sided *P*-value falls below 0.0115. Otherwise, the study is continued with a second stage, and the null hypothesis is rejected in the final analysis if the product of the stage-wise one-sided *P*-values falls below 0.0038.

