## Background

In Germany, more than 700,000 open abdominal operations (laparotomies) are performed each year [1]. A major surgical complication after laparotomy is abdominal fascia dehiscence, which may appear either as an early (burst abdomen with evisceration) or a late (incisional hernia) complication. These patients usually undergo surgery for secondary fascial closure, which is associated with markedly increased morbidity [2], including high recurrence rates (up to 45%) [3]. The applied surgical strategy for abdominal wall closure (that is, the combination of suture technique and material) is of high relevance for the prevention of fascia dehiscence and, moreover, constitutes the main factor directly controllable by the surgeon. However, a recent cross-sectional study among surgeons at institutions participating in a large multicenter trial revealed a lack of consensus regarding abdominal wall closure strategies [4]. In particular, there is uncertainty regarding optimal abdominal wall closure in patients undergoing an emergency laparotomy. Several randomized controlled trials (RCTs) as well as meta-analyses have addressed the issue of optimal fascia closure in elective laparotomies [2,5-12]. Yet, there have been no RCTs dealing exclusively with the emergency setting. As a result, abdominal fascia closure is performed according to the surgeon’s individual preference rather than according to evidence-based data. The present RCT is designed to compare the most established strategies (continuous slowly absorbable sutures and interrupted rapidly absorbable sutures) for abdominal wall closure after midline incisions for emergency laparotomy to determine the superiority of either strategy regarding the development of incisional hernia.

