#### ***Determination of the sample size***

The sample size calculation is based on the two-sided chi-square test for difference for the assessment of the primary endpoint. It can be expected that taking the potential confounders BMI and age into account in the analysis will increase the power as compared with the chi-square test. Due to the lack of any empirical data on the overall rate and the treatment effect to be expected, only a preliminary sample size calculation is performed and a sample size reassessment is conducted in a planned adaptive interim analysis (see above). The power for early rejection of the null hypothesis after the first study stage with a total of 80 evaluable patients amounts to 80% if, for example, the true incidence rates of incisional hernia or burst abdomen are 0.20 and 0.53 or 0.30 and 0.65, respectively, in the two groups.

A sample size of 80 evaluable patients until the interim analysis was therefore considered as both feasible and sufficient to gain enough information required for sample size recalculation in case the trial is continued after the interim analysis. The rate of loss to follow-up observed up to the interim analysis will also be taken into account when calculating the sample size for the second stage.

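### The interim and final rules use a one-sided p-value with no stated direction, while the aim, the null hypothesis and the sample-size test are two-sided

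*Protocol article*

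**What the plan says.** The Protocol article frames its question without a direction. The Background section gives the purpose as "to determine the superiority of either strategy regarding the development of incisional hernia". The Hypothesis section says that "the null hypothesis tested is that there is no difference in the incidence of burst abdomen" or hernia between the two strategies. The section on determination of the sample size says: "The sample size calculation is based on the two-sided chi-square test for difference".

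The decision rules in the Interim analysis section are one-sided: "The global one-sided type I error rate of the trial is controlled by 0.025". Three bounds follow:
- "The study is stopped after the interim analysis with acceptance of the null hypothesis if the one-sided" p-value is above 0.40;
- the null is rejected early if that p-value is below 0.0115;
- otherwise a second stage follows, and the null is rejected if the product of the two stage-wise one-sided p-values is below 0.0038.

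No section names the favoured closure. The Data analysis section gives only the contrast, continuous against interrupted. The sample-size section gives pairs of rates without assigning them to arms. The Discussion points both ways: it reports pooled evidence in favour of continuous suture, and it offers a rationale for interrupted closure whose superiority, it says, a trial must assess.

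**The concern.** A one-sided p-value is undefined until its alternative is named. In a fixed design with only a rejection bound this is often harmless shorthand for half of a two-sided test. Here it is not, because of the 0.40 bound. In a single direction, p above 0.40 covers two very different results: little signal either way (p between 0.40 and 0.60) and a strong signal for the other closure (p near 1). Both would end the trial with the null accepted.

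The product test also depends on direction, since it makes sense only if both stages test the same alternative. So the rule that decides whether the trial ends, and what it concludes, can be read in two ways with very different results.

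**Working it through.** **Inputs.** Bounds 0.40, 0.0115 and 0.0038 and the global one-sided 0.025 (Interim analysis). 80 evaluable patients at stage 1; rates 0.20 vs 0.53 and 0.30 vs 0.65; stated power 80% (Determination of the sample size). Assumptions: 40 per arm, from the balanced blocks, and an unadjusted pooled z-test in place of the planned logistic model with BMI and age.

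**1. The plan's constants.** Product bound: c = exp(−χ²(0.975; 4 df)/2) = exp(−11.143/2) = 0.0038. Overall one-sided level: 0.0115 + 0.0038 × ln(0.40/0.0115) = 0.0115 + 0.0038 × 3.549 = 0.0250. Both reproduce.

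**2. The plan's power.** Power = Φ((Δ − z·s₀)/s₁), with z = 2.273 for one-sided 0.0115, s₀ the pooled and s₁ the unpooled standard error.
- 0.20 vs 0.53: (0.33 − 2.273 × 0.1077)/0.1011 gives 80.0% (exact enumeration 81.5%).
- 0.30 vs 0.65: (0.35 − 2.273 × 0.1117)/0.1046 gives 82.1% (exact 80.9%).

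The stated 80% is confirmed. It cannot show which reading is meant, because one-sided 0.0115 and two-sided 0.023 give the same power. Reading 0.0115 as a two-sided level gives 71.7% and 74.2%, which does not match.

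**3. Reading A: one fixed direction, and the other closure is better.** Probability that the stage-1 one-sided p exceeds 0.40, by exact binomial enumeration:

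| True rates (the closure not favoured by the test is better) | Stops with acceptance |
|---|---|
| 0.20 vs 0.53 | 99.98% |
| 0.30 vs 0.65 | 99.98% |
| 0.25 vs 0.40 | 96% |
| 0.20 vs 0.30 | 89% |

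Example: 21/40 against 8/40 events. The difference is 0.325, the pooled rate 29/80 = 0.3625, the standard error 0.1075 and z = 3.02. The two-sided p is 0.0025, but the one-sided p in the tested direction is 0.9988, so the rule accepts the null.

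**4. Reading B: both directions, with stage 2 keeping the stage-1 direction.** Acceptance needs both one-sided p-values above 0.40, that is, p between 0.40 and 0.60 or two-sided p above 0.80. At 0.20 vs 0.53 this has probability 0.2%. The example above is rejected early, since 0.00125 is below 0.0115. The two directions cannot both reject, so the error rate for claiming that either closure is better is 2 × 0.0250 = 0.050 (simulation of 4 million trials: 0.0501).

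**5. Stopping when there is no difference.** At a common rate of (0.20 + 0.53)/2 = 0.365, exact enumeration gives early acceptance in 63% of trials under reading A and 26% under reading B. The continuous approximation is 60% and 20%.

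**The case against.** The best defence is that one-sided 0.025 is the usual counterpart of two-sided 0.05, and that the aim, the null and the sample-size test all point to symmetric use with 0.0115 in each tail. On that reading the damaging acceptance almost never happens. The article is also condensed, and the full protocol or the SAP may define the p-value.

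Much of this stands. The 99.98% depends on fixing one direction, which the text does not do, so it is not a forecast of what the trial will do. An overall 0.050 is the ordinary two-sided level; it is a different quantity from the stated 0.025, not a loss of error control. The mismatch remains, however: the article prints the full rules with exact bounds on a one-sided p-value beside a two-sided question, and nowhere says that they run in both directions.

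A reader might go further in two ways that the documents do not support. One is that the direction could be chosen afresh at each stage, raising the error above 0.05. That requires multiplying p-values for opposite alternatives, and nothing in the article suggests it. The other is that "The study is stopped after the interim analysis with acceptance of the null hypothesis" amounts to a claim of equivalence. It labels a stopping outcome, and the article makes no such claim.

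**Conclusion.** The point holds as a contradiction about sidedness within the article. The arithmetic of the design is correct, but the direction of the p-value that drives all three rules is not stated and does not follow from the rest of the text.

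The consequence depends on the reading. With one fixed direction, the trial would stop with the null accepted about 99.98% of the time when the other closure is better by the protocol's own rates, and 89% of the time at 0.20 vs 0.30. With symmetric use, acceptance at 0.20 vs 0.53 is about 0.2%, and 0.025 is the error rate per direction, with 0.050 for a claim in favour of either closure. It would be too strong to say that the trial cannot answer its question, because the symmetric reading does answer it.

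The figures assume 40 per arm and an unadjusted test. The adjusted logistic model would shift them somewhat, but it would not remove the gap between the two readings.

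**What to change.** Before the interim analysis, state that:
- the rules apply separately to each direction (continuous better; interrupted better), each at one-sided 0.025 with the existing constants, for an overall two-sided level of 0.05;
- the null is rejected early for a direction if its stage-1 p is below 0.0115;
- the trial stops for futility only if both stage-1 one-sided p-values exceed 0.40 (two-sided p above 0.80);
- otherwise the direction with stage-1 p at or below 0.40 goes forward, and the product test uses that same direction in stage 2.

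At most one direction can go forward, since the two p-values sum to 1. If the sponsor does intend a single direction, it should name it and bring the aim, the null and the sample-size text into line, accepting that superiority of the other closure could then not be shown.

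The cost is wording only; the constants, the stage-1 size and the stated power stay as they are. The overall level must be declared as two-sided 0.05, and fewer trials with no true difference would stop early (about 26% instead of 63% at a common rate of 0.365), so a second stage becomes more likely. The wording must be settled before interim outcomes are seen.

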#### ***Data analysis***

For the interim analysis as well as for the final analysis, each patient’s allocation to the different analysis populations (full analysis set (FAS), per protocol (PP) analysis set, safety analysis set) will be defined prior to the analysis. The allocation will be documented in the statistical analysis plan. During the data review, deviations from the protocol will be assessed as ‘minor’ or ‘major’. Major deviations from the protocol will lead to the exclusion of a patient from the PP analysis set.

The null hypothesis is assessed by testing the effect of the wall closure procedure (continuous versus interrupted) in a logistic regression model that takes into account the covariates body mass index (BMI; values as measured on the original scale) and age (values as measured on the original scale). The decision rules according to the adaptive design as specified above will be applied in the interim and the final analysis, respectively.

Confirmatory analysis will be primarily based on the FAS, which is consistent with the intention-to-treat principle by including all patients who were randomized to the two groups. This approach reflects the idea that the study should match as closely as possible to the conditions in clinical practice.

If a patient leaves the study prematurely, missing data with respect to the primary outcome variable will be replaced by the Imputed Case Analysis by incorporating available reasons for missing data (ICA-r) method described by Higgins *et al*. [22].

In addition to the evaluation of the FAS, a PP analysis will be performed for the primary endpoint including all randomized patients without major protocol violations. The secondary variables will be analyzed descriptively by tabulation of the measures of the empirical distributions and by application of appropriate tests whose results are to be interpreted in a strictly descriptive sense.

#### ***Determination of the sample size***

The sample size calculation is based on the two-sided chi-square test for difference for the assessment of the primary endpoint. It can be expected that taking the potential confounders BMI and age into account in the analysis will increase the power as compared with the chi-square test. Due to the lack of any empirical data on the overall rate and the treatment effect to be expected, only a preliminary sample size calculation is performed and a sample size reassessment is conducted in a planned adaptive interim analysis (see above). The power for early rejection of the null hypothesis after the first study stage with a total of 80 evaluable patients amounts to 80% if, for example, the true incidence rates of incisional hernia or burst abdomen are 0.20 and 0.53 or 0.30 and 0.65, respectively, in the two groups.

A sample size of 80 evaluable patients until the interim analysis was therefore considered as both feasible and sufficient to gain enough information required for sample size recalculation in case the trial is continued after the interim analysis. The rate of loss to follow-up observed up to the interim analysis will also be taken into account when calculating the sample size for the second stage.

## Discussion

The optimal strategy of abdominal wall closure after midline laparotomy has remained an issue of ongoing discussion. To date, various RCTs and meta-analyses on abdominal wall closure strategies after midline laparotomy have been published with heterogeneous results. A recent meta-analysis identified several RCTs on techniques and materials of abdominal wall closure after elective laparotomy [20]. While some of the detected studies included patients who underwent emergency laparotomy, there were no trials that specifically enrolled patients who had emergency surgery. The pooled analyses demonstrated a benefit of the continuous suture technique on the development of incisional hernia. Remarkably, statistical heterogeneity of the meta-analyses increased substantially if studies that enrolled patients with emergency laparotomy were included, whereas there was almost no heterogeneity in the sensitivity analyses excluding these studies. These findings suggest a significant difference between the biological properties of and demands to the abdominal wall of patients undergoing elective and emergency laparotomy. Reasons for this difference have not been clarified in detail and probably include factors such as a contaminated operative field, poor general conditions of these (septic) patients and different requirements to the abdominal wall, especially in patients requiring prolonged mechanical ventilation. In particular, the proliferation of bacteria in tissue represents a strong risk factor causing wound infection with delayed healing of the wound and wound dehiscence [23]. The adverse impact of emergency surgery on the incidence of postoperative complications as compared to an elective setting has already been demonstrated in various studies [24-28]. In a large cohort study including more than 4.800 patients who underwent open gastrointestinal surgery, emergency surgery was associated with a significantly increased incidence of postoperative tissue and wound complications [24]. On multivariate analysis, male gender, peritonitis, kind of operation and multiple operations were independent predictors of tissue and wound complications in the subgroup of patients who underwent emergency surgery.

Based on the described differences between patients undergoing emergency and elective laparotomy as well as the current lack of studies, there is an urgent need for prospective studies specifically assessing strategies of abdominal wall closure after emergency midline laparotomy The present RCT compares the two most commonly applied strategies of abdominal wall closure after midline laparotomy, that is, the continuous, all-layer suture technique using slowly absorbable monofilament material (two Monoplus® loops) and the interrupted suture technique using rapidly absorbable braided material (Vicryl® sutures). The incidence of burst abdomen by 30 days or incisional hernia within 12 months after surgery was chosen as the primary endpoint to specifically assess the impact of both closure techniques on abdominal fascia healing in the emergency setting. In theory, the interrupted closure technique may allow discharge of (contaminated) ascites and thus be associated with fewer intra-abdominal complications (for example, fluid collections or abscess) as well as improved abdominal fascia healing. However, a randomized trial is required to validly assess superiority of this technique.

An adaptive interim analysis is performed in the CONTINT trial to cope with the lack of reliable data required for a substantiated sample size calculation.

To achieve a homogenous study population, only patients undergoing primary midline laparotomy for an emergency indication will be included in the CONTINT trial. Furthermore, the confirmatory analysis of the overall treatment effect is performed using a logistic regression model that includes patients’ BMI and age as potential confounding factors. There is a recognized need to standardize the definition of complications after surgical interventions to enable comparisons of results from different studies [29-31]. For this reason, endpoints within the CONTINT trial have been defined *a priori* to minimize assessment bias.

In conclusion, the CONTINT trial represents the first RCT assessing efficacy and safety of two different abdominal wall closure strategies in patients undergoing emergency midline laparotomy. Applying high methodological standards, the results of the trial will help to improve and standardize surgical treatment in this specific population of patients that may not be simply compared to patients undergoing elective surgery.

## Trial implementation and status

### Protocol development and trial organization

The CONTINT trial has been designed initially as a single center RCT and was initiated at the Department of Surgery, University of Heidelberg in November 2007. After 1.5 years of recruitment, a total of 16 patients had been enrolled in the study. Due to the insufficient recruitment of patients at a single center, we decided to expand the number of trial institutions, including distribution via the Trial Network of the German Surgical Society (CHIR-*Net*). Consequently, the trial protocol was amended and an investigators’ meeting was held at Frankfurt, Germany on 31 August 2009. Up to this date, 26 patients had been recruited.

A total of 11 trial centers have approved participation in the CONTINT trial. A total of 73 patients have been randomized at the date of submission of this paper.
